#### Endline assessment

Endline assessment of outcomes will be undertaken after completion of 12-month follow-up. The assessments will be carried out by independent outcome assessors inviting the participants to camps and mop up will be organised through home visits.

#### Data management

This study has only electronic version of the study forms and the dataset automatically synchronises with the server. There are built‐in data checks and further data cleaning will be done by trained data managers at Public Health Foundation of India (PHFI), under the supervision of the Principal Investigator. All electronic data are encrypted, password protected and stored in secure computer networks.

Data are monitored centrally for its quality and completeness using electronic validation and on-site monitoring. Recruitment and retention of participants was assessed by examining the number eligible for recruitment, number enrolled in the study and dropout from regular follow-up will be assessed at the completion of 12 months. In addition, we are carrying out central statistical monitoring (CSM) all through the trial. CSM aims to detect outliers and inliers, deviation of any cluster from the average and to detect potential data error or incorrect data collection procedure. Field coordinators undertake monthly visits to all sites, record their observations using Objective Systematic Structured Observations (OSSO) checklist regarding intervention delivery, source documents examination, protocol adherence and adverse event recording and reporting. The monthly visit reports are sent online to the research coordinating centre. In addition, study investigators undertook site visits to monitor enrolment process, intervention delivery and protocol adherence and reported to the trial management committee.

#### Statistical methods

Quantitative data analysis will be performed using STATA V. 13.0 (Stata). A statistical data analysis plan will be prepared and discussed with Data Safety Monitoring Board (DSMB) before data collection is completed.

The primary analyses will be conducted under the principle of intention to treat. All randomised participants will be analysed in the groups to which they were originally allocated to, regardless of whether they actually retained that specific group membership over the course of the trial or not. Participants who withdrew consent for use of their data will not be included in any analyses.

Demographic and clinical characteristics will be examined for participants at each CHC. Summaries will be presented as means and SD of those variables that are approximately normally distributed, or medians and IQRs for skewed variables. Categorical variables will be summarised as frequencies and percentages. Transformations will be used when distributional assumptions are not fulfilled for inferential tests on a continuous measure. If we find a considerable imbalance in some variables at baseline, we will consider adjusting for these variables by including them in the model to estimate the effect of the intervention. In principle, in a trial with individual blinded randomisation, there should be no major baseline differences between arms, but this may not be the case in cluster sample given that the number of samples are small, individuals are not completely blind. So there is some potential for baseline differences between individuals recruited in each arm and this will have to be adjusted for in the analysis.

We will also account for the influence of clustering at the CHC level on the outcome. Data will be analysed at the individual level and comparisons will be made between the mean changes in the primary outcomes in the intervention and control groups. Linear-mixed effect models adjusting for baseline measurements will be used with a random intercept for the CHC level to account for the clustering in the data.

Reporting of results will be in accordance with the principles of Consolidated Standards of Reporting Trials(CONSORT) statements extended for cluster randomised controlled trial (RCT).

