### Recruitment

For the two primary outcomes (SBP and HbA1c), we planned to recruit a total of 90 participants per site with a minimum of 45 participants with each conditions: hypertension and diabetes. We estimated that the recruitment could be completed in 2 months enrolling a minimum of two to three participants a day. However, some sites had lower recruitment rate for either of the two conditions. Therefore, the final strategy was to stop recruitment of participants with either condition after reaching 45, and then complete recruitment of patient with the other condition. A total of 3702 participants were recruited from 40 CHCs.

All individuals diagnosed to have hypertension and/or type 2 diabetes were assessed for eligibility by the nurse. All eligible participants were invited to participate in the trial. After providing written and verbal information about the trial, written consent was obtained by the nurse. The flow of trial participant is depicted in figure 1.

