### Randomisation

Randomisation units are clusters (CHCs). The randomisation list was generated by a statistician independent of the trial using STATA SE V. 12. The list was stratified by states (Haryana and Karnataka) and within states by availability/non-availability of nurses recruited under NPCDCS. In Karnataka, stratification based on availability of nurses was done allocating 10 clusters in each category (nurse available under NPCDCS/not available). In Haryana, as there was no nurses recruited under NPCDCS, further stratification was not done. Clusters (CHCs) within each strata were randomised to intervention or enhanced care arm using block randomisation (with a block size of 2). Being a cluster randomised trial, only limited blinding could be enforced. The study statistician will remain blinded throughout the study until database is locked and study unblinded.

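### Covariates beyond baseline measurements enter the primary model by observed imbalance, optional in one sentence and required in another; a fixed adjustment set should replace this

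*Protocol article*

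**What the plan says.** All of the analysis text is in the Statistical methods section of the protocol article.

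- **Fixed part of the model:** "Linear-mixed effect models adjusting for baseline measurements will be used with a random intercept for the CHC level". I read the baseline measurements as the baseline value of the outcome being analysed. This adjustment is unconditional.
- **Further covariates, optional:** "If we find a considerable imbalance in some variables at baseline, we will consider adjusting for these variables by including them in the model". No threshold is attached, and the commitment is only to consider adjustment.
- **Further covariates, required:** two sentences later, "So there is some potential for baseline differences between individuals recruited in each arm and this will have to be adjusted for in the analysis".
- **Safeguards:** "A statistical data analysis plan will be prepared and discussed with Data Safety Monitoring Board (DSMB) before data collection is completed". The Randomisation section adds: "The study statistician will remain blinded throughout the study until database is locked and study unblinded".

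Three other sections bear on whether recruitment could differ by arm. The Randomisation section makes CHCs the randomised units and says: "Being a cluster randomised trial, only limited blinding could be enforced". The Recruitment section says: "All individuals diagnosed to have hypertension and/or type 2 diabetes were assessed for eligibility by the nurse"; the nurse also took consent. The Participant timeline section has the intervention start at the first visit, which is the enrolment visit.

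**The concern.** The protocol does not simply leave the covariate list to a later document. It states a selection rule, and the rule is poorly set in three ways.

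1. **It contradicts itself.** An analyst cannot both treat adjustment as optional and treat it as required.
2. **It uses the wrong criterion.** An omitted covariate distorts the estimate in proportion to its imbalance multiplied by its relation to outcome. Selecting on imbalance alone can leave out a strongly prognostic variable with modest imbalance and bring in an imbalanced variable that predicts nothing. It also gives up the precision available from prognostic variables that happen to be balanced.
3. **It makes the remedy for differential recruitment discretionary.** The protocol itself foresees baseline differences between the individuals recruited in each arm.

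At stake are the reproducibility of the primary estimate, some precision and, if recruitment did differ by arm, a residual bias in SBP and HbA1c.

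**Working it through.** The plan gives no figure on this point to reproduce. The documents supply SD 15 mm Hg, target difference 4 mm Hg, ICC 0.05, 40 participants per cluster with 20% loss (so 32) and 40 clusters (20 per arm), all from the Sample size calculation section. The covariate ICC, imbalance threshold, recruitment shift and covariate-outcome correlation are **assumptions**.

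**Step 1. Chance imbalance.** For a covariate measured on about 90 participants per CHC, the SD of the standardised difference between arms is sqrt(2 × (1 + 89 × ICC) / 1800).

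| Assumed covariate ICC | SD of difference | P(difference beyond 0.1 SD) |
|---|---|---|
| 0.02 | 0.056 | 7% |
| 0.05 | 0.078 | 20% |
| 0.10 | 0.105 | 34% |

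A 0.1 SD imbalance on a covariate with correlation 0.3 to SBP change shifts the estimate by 0.1 × 0.3 × 15 = 0.45 mm Hg, or 11% of 4 mm Hg. The standard error from the document's inputs is sqrt(2 × 15² × (1 + 31 × 0.05) / (32 × 20)) = 1.34 mm Hg, so this shift is 0.45 / 1.34 = 0.34 of a standard error. Chance imbalance is random error, already reflected in that standard error. It is not bias. (This standard error implies power of about 85%, not the stated figure of over 98%. That is a separate matter on which this point does not rest.)

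**Step 2. How often the rule would act.** With 32 per cluster and covariate ICC 0.05, the SD of the difference is sqrt(2 × (0.05 + 0.95/32) / 20) = 0.0893. With an assumed threshold of 0.2 SD and no recruitment difference, one covariate triggers the rule with probability 2.5%, and at least one of ten independent covariates with probability 1 − (1 − 0.025)^10 = 22%.

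**Step 3. Bias left by the rule if recruitment differs.** Let the true shift be 0.15 SD and the partial correlation 0.4.

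- Never adjusting: 0.15 × 0.4 × 15 = 0.90 mm Hg.
- Under the rule, bias remains only in trials where the observed difference stays within 0.2 SD. With z = (0.2 − 0.15) / 0.0893 = 0.56, the mean contribution is 0.15 × Φ(0.56) − 0.0893 × φ(0.56) = 0.15 × 0.712 − 0.0893 × 0.341 = 0.076 SD (the lower tail is negligible). Then 0.076 × 0.4 × 15 = 0.46 mm Hg.
- On HbA1c (SD 1.1, target 0.37) the same case gives 0.076 × 0.4 × 1.1 = 0.03 percentage points, about 9% of the target.

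**Step 4. Simulation.** 20,000 trials per scenario at cluster level, true effect zero. Cells show mean SBP bias in mm Hg and type I error.

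| Shift (SD) | Correlation | Never adjust | Imbalance rule | Always adjust |
|---|---|---|---|---|
| 0 | 0.2 | −0.01, 5.2% | −0.01, 5.1% | −0.01, 5.0% |
| 0 | 0.4 | 0.00, 5.1% | 0.00, 4.8% | 0.00, 5.1% |
| 0.10 | 0.2 | 0.29, 5.5% | 0.19, 5.1% | −0.01, 5.0% |
| 0.10 | 0.4 | 0.59, 7.0% | 0.41, 5.5% | 0.00, 5.1% |
| 0.15 | 0.2 | 0.46, 6.3% | 0.24, 5.4% | 0.00, 5.1% |
| 0.15 | 0.4 | 0.90, 10.1% | 0.46, 6.2% | 0.00, 5.0% |
| 0.20 | 0.2 | 0.60, 7.3% | 0.19, 5.3% | 0.00, 5.0% |
| 0.20 | 0.4 | 1.20, 14.0% | 0.39, 6.4% | 0.00, 5.4% |

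The simulation agrees with the hand calculation. The rule reduces the bias from a measured covariate without removing it. It does no harm when there is no shift.

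**The case against.** Much can be said for the plan, and most of it stands against stronger readings of this point.

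- **A reader might infer that no covariate is adjusted for unless imbalance is seen.** The text does not support that: baseline measurements are in the model in every case. The point concerns further covariates only.
- **A reader might infer that recruitment bias goes uncorrected.** The protocol names the possibility and says it must be adjusted for. In the shifted scenarios above, the rule removes between about 30% (0.59 to 0.41) and two thirds (1.20 to 0.39) of the bias from a measured covariate. No covariate list removes bias from unmeasured factors.
- **A reader might infer that the model stays open until outcomes are seen.** An analysis plan is due before data collection ends, and the statistician is blinded until database lock. What remains is weaker. Recruitment was already complete, so the plan could be written with baseline data in view, and no sentence ties the imbalance judgement to a time before unblinding.
- **A reader might take it as stated that the enrolling nurses knew the allocation.** No section says so. It is a reasonable inference from cluster randomisation, nurse enrolment, limited blinding and an intervention that began at the enrolment visit. The protocol itself speaks only of some potential for differences.
- **The covariate list may properly be left to the analysis plan.** Agreed, and its absence is not the finding. The same holds for the strata, which the model sentence does not name. The finding is the rule that the protocol does state, and its conflict with the sentence that follows.

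**Conclusion.** The point holds in a limited form and is worth correcting. The protocol selects further covariates by an undefined degree of observed imbalance, and its two sentences disagree on whether adjustment then follows. The criterion ignores prognostic value and gives up precision.

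The size of any harm is modest and conditional. Without differential recruitment there is no bias, and type I error stays at about 5%. With it, the residual SBP bias across the scenarios run is 0.19 to 0.46 mm Hg, at most about 11% of the 4 mm Hg target, and type I error is 5.1% to 6.4%. At correlation 0.2 the inflation is barely visible (5.1% to 5.4%).

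These figures rest on an assumed 0.2 SD threshold, shifts of 0.10 to 0.20 SD, correlations of 0.2 and 0.4, and covariate ICC 0.05. They also use the full 15 mm Hg SD of change; if baseline adjustment leaves a smaller residual SD, they shrink in proportion. The documents give no evidence that recruitment did differ by arm, or by how much.

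**What to change.** 1. Reconcile the two sentences in Statistical methods so that adjustment does not depend on observed imbalance.
2. Before unblinding, and preferably without reference to baseline comparisons by arm, name one adjustment set for the primary model and apply it whatever the imbalance:
   - baseline value of the outcome (already planned);
   - randomisation stratum, that is, state and, within Karnataka, availability of a nurse recruited under the national programme;
   - age and sex;
   - enrolment condition (hypertension, diabetes or both).
3. Keep any model with covariates chosen by imbalance as a labelled sensitivity analysis.
4. State that adjustment addresses measured differences only.

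**Cost.** The data are already collected in both arms, so the change is one of wording. The three strata (Haryana, and two in Karnataka) use about 2 of the 38 cluster-level degrees of freedom (40 clusters − 2 arms). The other terms use a few at participant level, which is negligible with 3702 recruited.

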### Trial design

mWellcare is a cluster randomised controlled trial with equal allocation of participants between intervention and enhanced care arms.

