### Study setting

Twenty clusters each from two states: one in the north and the other in the south India have been selected for the trial. Each cluster is a Community Health Centre (CHC) which caters to a rural population of 120 000 and serves as a referral centre for four Primary Health Centres (PHCs) in the formal healthcare delivery system.^20^ CHCs were selected from districts covered under the NPCDCS. Allocation of the CHCs into intervention and control arm is described in the section on randomisation.

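### The stated primary mixed model does not name the three strata used to randomise CHCs; if those strata predict outcome, its standard errors are too large and the test is conservative

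*Protocol article*

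**What the plan says.** The Randomisation section of the protocol article describes the allocation of CHCs: "The list was stratified by states (Haryana and Karnataka) and within states by availability/non-availability of nurses recruited under NPCDCS". For the southern state it adds: "In Karnataka, stratification based on availability of nurses was done allocating 10 clusters in each category". In Haryana there were no nurses recruited under the programme, so "further stratification was not done". The Study setting section gives the number per state: "Twenty clusters each from two states: one in the north and the other in the south India". Together these make three strata of 20, 10 and 10 CHCs. Within each stratum, CHCs were allocated "using block randomisation (with a block size of 2".

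The Statistical methods section describes the primary model: "Linear-mixed effect models adjusting for baseline measurements will be used with a random intercept for the CHC level to account for the clustering". It names two components, baseline and a CHC random intercept. The same section says that adjustment will be considered for variables found to be considerably imbalanced at baseline. It also says that a separate analysis plan will be prepared and discussed with the DSMB before data collection ends. State and nurse availability do not appear in the description of the analysis.

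**The concern.** An analysis should normally reflect the restrictions placed on the randomisation. Blocks of 2 in strata of even size give equal numbers of CHCs per arm in every stratum, so differences between strata cancel out of the comparison of arms. A model without the strata still counts those differences as between-CHC variance and carries them into the standard error of the treatment effect. The reported uncertainty then exceeds the true uncertainty: confidence intervals are too wide, the test rejects less often than its nominal level, and precision that the design has already bought goes unused.

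The covariate rule does not close the gap. It reacts to imbalance, and the strata are balanced at CHC level by construction. Followed as written, the plan could adjust for variables chosen after looking at the data while omitting the factors fixed before allocation.

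**Working it through.** The plan gives no figure for the effect of the strata, so there is none to reproduce. The power at a zero share below is a working baseline for comparing the two models. How it relates to the power stated in the sample size section is a separate question and is not used here.

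**Inputs from the Sample size calculation section.** SBP: difference 4 mm Hg, SD of change 15, ICC 0.05. HbA1c: difference 0.37, SD 1.1, ICC 0.04. Both: 40 recruited per CHC and 20% loss, so 40 × 0.8 = 32 analysed, and 40 CHCs, so 20 per arm.

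**Assumptions.** Two-sided 5% test, normal approximation, equal cluster sizes. The stated ICC is taken to include any between-stratum variance. The share *s* of between-CHC variance explained by the strata is not in the documents and is varied.

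**Balance.** Strata of 20, 10 and 10 in blocks of 2 split 10:10, 5:5 and 5:5.

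**Variance of a CHC mean, SBP.**
- Between CHCs: 0.05 × 15² = 11.25.
- Within: 0.95 × 15² / 32 = 213.75 / 32 = 6.68.
- Total: 17.93.

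**Standard errors.**
- Model without strata: √(2/20 × 17.93) = 1.339, whatever *s* is.
- True SE, which the model with strata targets: √(2/20 × (11.25(1 − s) + 6.68)).
- r = true SE / 1.339.

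**Operating characteristics.**
- Type I error without strata: 2Φ(−1.96 / r).
- Power without strata: Φ((4/1.339 − 1.96) / r).
- Power with strata: Φ(4/(1.339 r) − 1.96).

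| Assumed share s | True SE | r | Model SE too large by | Type I error, no strata | Power, no strata | Power, with strata |
|---|---|---|---|---|---|---|
| 0% | 1.339 | 1.000 | 0% | 5.0% | 85% | 85% |
| 10% | 1.296 | 0.968 | 3% | 4.3% | 86% | 87% |
| 20% | 1.252 | 0.935 | 7% | 3.6% | 86% | 89% |
| 30% | 1.206 | 0.901 | 11% | 3.0% | 87% | 91% |
| 50% | 1.109 | 0.828 | 21% | 1.8% | 89% | 95% |

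**Simulation check.** Forty CHC means in strata of 20/10/10 with blocks of 2 were simulated, with 20,000 runs per scenario. At a 25% share, type I error was 3.2% without strata and 4.7% with them, and power 84.4% and 88.2%. At 50%, type I error was 1.8% and 5.0%, and power 87.0% and 94.1%. The pattern matches the table.

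**HbA1c.** The variance of a CHC mean is 0.04 × 1.1² + 0.96 × 1.1² / 32 = 0.0484 + 0.0363 = 0.0847, so the model SE is √(2/20 × 0.0847) = 0.092. At shares of 10% and 50% the SE is 3% and 18% too large. Power without and with strata is 98.3% and 98.5% at 10%, and 99.3% and 99.7% at 50%. The difference is under 1 point throughout.

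**Cost if the strata explain nothing.** A cluster-level t comparison goes from 38 to 36 degrees of freedom. The critical value rises from 2.024 to 2.028, or 0.2%, and SBP power falls by about 0.1 point.

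**The case against.** The strongest objection is that this is a condensed article which announces a separate analysis plan, and a full covariate list is commonly left to such a plan. A reader might infer that the investigators decided to exclude the strata. The text does not support that: it does not name them, and it does not rule them out. What remains is that the article does commit to a covariate set, a random-effects structure and a rule for further covariates. None of these leads to the strata, although the randomisation is described in detail.

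A reader might also infer that the intervals will certainly be too wide. That does not follow. At a zero share there is no error, and at 10% the SE is only 3% too large. The Discussion makes a place effect plausible, since drugs are supplied by state governments and availability varies, but it refers to districts as well as states. Variation between districts within a stratum would not be removed by stratum terms.

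Nor is this a validity threat in the usual sense. The stratum effect causes no bias and no excess of false positives. Power under the model without strata does not fall below its zero-share value; what is lost is the further gain that the strata would allow.

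Finally, a reader might infer a small-sample inflation of type I error because no reference distribution is named. The article fixes neither the estimation method nor the reference distribution, and naming Stata as the software settles neither. Those choices normally belong in the analysis plan. They would act separately from the stratum effect and are no part of this point.

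**Conclusion.** The point holds in conditional form. As described, the primary model names baseline and a CHC random intercept but not the three randomisation strata, and the imbalance rule would not add them. If the strata predict change in SBP or HbA1c, the standard error is too large and the test conservative.

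For SBP, the overstatement of the SE runs from nil to about 21% as the assumed share goes from 0 to 50%, and the power forgone runs from nil to about 6 points. For HbA1c the intervals would also be too wide, but the loss of power is negligible. These sizes rest on the plan's SDs and ICCs, 32 analysed per CHC, equal cluster sizes, a normal approximation, and a stratum share that the documents do not give. The change is worth making because it costs almost nothing and aligns the analysis with the randomisation, not because a large loss has been shown.

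**What to change.** State in the analysis plan, before unblinding, that the three-level randomisation stratum (Haryana; Karnataka with an NPCDCS nurse; Karnataka without one) enters the primary SBP and HbA1c models as a fixed effect, whatever the baseline comparison shows. Do the same in the corresponding secondary models. Keep baseline and the CHC random intercept as they are.

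The cost is a sentence in the plan and two cluster-level degrees of freedom. The stratum of every CHC is already known from the randomisation list, so no new data are needed.
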